# FocaL mass drug administration for *Plasmodium vivax *malaria elimination (FLAME): study protocol for an open-label cluster randomized controlled trial in Peru

**DOI:** 10.1186/s13063-025-09112-1

**Published:** 2025-10-14

**Keywords:** Chemoprevention, Tafenoquine, Primaquine, Glucose 6 phosphate dehydrogenase deficiency, Cluster randomized control trial, Peru, Malaria, *Plasmodium vivax*

## Abstract

**Background:**

Outside of sub-Saharan Africa, *Plasmodium vivax* has become the dominant species of malaria. Focal mass drug administration (fMDA) is a potential strategy to support elimination efforts, but controlled studies are lacking.

**Methods:**

The FocaL mass drug Administration for *Plasmodium vivax* Malaria Elimination (FLAME) study is a 3-year cluster randomized controlled trial to determine the impact and safety of fMDA to reduce *P. vivax* transmission. The study will be conducted in Loreto, Peru, where standard interventions have reduced *P. vivax* cases, but transmission persists due to a high proportion of subclinical infections. Thirty low transmission communities (API < 250 cases/1000 population) will be randomized 1:1 to fMDA versus control using a restricted randomization. All communities will receive Peruvian national standard malaria control measures. In the intervention arm, high-risk individuals (living within 200 m of a *P. vivax* case reported in the prior 2 years) without contraindication to study medications, including G6PD deficiency, will receive three cycles of fMDA over a 2-year period. Each cycle will include two rounds of directly observed therapy delivered 2 months apart. The fMDA regimen will include 25 mg/kg chloroquine (CQ) plus a single 300 mg dose of tafenoquine (TQ) for individuals age ≥ 16 years, and 25 mg/kg of CQ plus 7 days of 0.5 mg/kg/day of primaquine (PQ) if younger. The primary outcome is the cumulative incidence of symptomatic *P. vivax* malaria. The sample size provides 80% power to detect at least a 68% relative reduction in cumulative *P. vivax* incidence, based on alpha of 0.05 and a coefficient of variation (*k*) of 0.87. Secondary outcomes include safety, cost-effectiveness, and infection prevalence and seroprevalence which will be assessed in annual cross-sectional surveys. Safety will be assessed in passive and active pharmacovigilance, including post-treatment screening for G6PD-associated hemolysis by assessing for anemia and hematuria in a sample.

**Discussion:**

The trial will generate evidence regarding fMDA for *P. vivax* and inform malaria elimination efforts in Peru and similarly endemic settings. Findings will be disseminated in peer-reviewed publications and through stakeholder meetings in Peruvian and international research forums.

**Trial registration:**

Clinicaltrials.gov NCT05690841. This trial was registered on 09 January 2023. Peruvian Clinical Trial Registry (REPEC) 020–23. This trial was registered on 21 February 2024.

**Supplementary Information:**

The online version contains supplementary material available at 10.1186/s13063-025-09112-1.

## Background

Current malaria control interventions disproportionally reduce malaria due to *Plasmodium falciparum*, leading to an increase in the proportion of malaria due to *Plasmodium vivax*. Outside of sub-Saharan Africa, *P. vivax* has become the predominant cause of malaria [1–3]. *P. vivax* presents unique challenges for malaria elimination [4]. As with *P. falciparum* malaria, subclinical infections do not come to the attention of the standard health care system. However, unlike *P. falciparum* which invades all red blood cells, *P. vivax* tends to invade reticulocytes, resulting in relatively lower density infections that can be missed by standard diagnostics. Untreated, *P. vivax* persists in its blood stage and remains latent in the liver as a hypnozoite, a stage that reactivates weeks to months later causing symptomatic attacks called relapses [5, 6].

Primaquine is the only widely available drug that kills *P. vivax* hypnozoites, but its widespread use is undermined by safety, adherence, and efficacy concerns [7]. Primaquine can trigger severe hemolysis in individuals with inherited glucose-6-phosphate-dehydrogenase (G6PD) deficiency [8]. Adherence to the prolonged 7−14 day treatment course is often poor [9], and even complete adherence to standard regimens can lead to recurrent episodes of malaria in approximately 20% of cases [10]. These challenges in case management limit the effectiveness of active case detection approaches [11] and contribute to a reservoir of infections that perpetuate ongoing community transmission.

Mass drug administration (MDA) is a strategy that clears infections that would not otherwise be detected and treated. This approach is focused on the provision of antimalarial treatment to a defined population, irrespective of the presence of symptoms or infection, often repeated at intervals. In 2015, the World Health Organization (WHO) recommended the use of MDA to reduce *P. falciparum* transmission in very low to low transmission settings, defined as areas where prevalence is less than 10% or incidence is less than 250 cases per 1000 population per year, where coverage of standard interventions is high, and risk of importation is low [1, 12]. A recent review of MDA for *P. falciparum* identified eight cluster randomized controlled trials (CRCT) showing short-term impact [13]. Sustained impact is more likely when baseline transmission intensity is lower, but in these settings where most of the population is not infected and a high proportion of infected individuals have minimal or no symptoms, the risks of adverse events following MDA may outweigh its benefits. Decreased perception of risk can also lead to poor acceptability and adherence [14, 15]. Limiting MDA to the highest risk groups can minimize these drawbacks, while still being effective. Reactive drug administration, or MDA directed at foci of household members and neighbors of index cases was studied in four recent CRCTs that demonstrated it to be effective for reducing community-level transmission of *P. falciparum* [13, 16]. The focal application of MDA to specific higher-risk subpopulations also facilitates higher coverage of MDA, efficient and cost-effective use of limited resources, and safety monitoring [17, 18]. However, the logistical challenges associated with delivery of MDA through this reactive, or “on-call,” approach may preclude its use in many settings.

For *P. vivax*, there are no published CRCTs of MDA using radical cure administered either at a village-level or focally. Anecdotal evidence suggests that large-scale mass drug administration to entire communities contributed to *P. vivax* elimination in temperate settings including Azerbaijan, Tajikistan, Afghanistan, North Korea, and China [19, 20]. However, more focal approaches may be an effective strategy that can address the logistical and safety challenges associated with MDA using radical cure—namely the long treatment courses and the potential for G6PD deficiency-associated hemolysis [18]. Most *P. vivax* cases are relapses [21, 22], and relapsing infections can persist for many months and even years. Hence, an obvious strategy would be target individuals harboring hypnozoites [21, 23]. In the absence of a convenient diagnostic test to detect hypnozoites [21, 24], an approach used in Central China was to conduct MDA annually in households of and near index cases reported from the prior 1–2 years. Specifically, focal MDA (fMDA) was conducted annually preceding the high transmission season, which was eventually followed by sustained interruption of *P. vivax* [20]. Operational advantages of this approach are that it self-tailors to changes in transmission levels and the program has time to prepare for delivery that is proactive rather than reactive. Despite lack of controlled data, the WHO made a conditional recommendation for the use of MDA to reduce *P. vivax* transmission given the urgent need for new approaches to eliminate malaria. At the same time, the WHO called for further research on its impact, operational factors, safety, and feasibility, particularly in tropical or subtropical settings [1, 25].

To generate evidence to inform global *P. vivax* elimination efforts, building on the approach used in Central China, we propose a trial to evaluate the impact and safety of fMDA directed at households in proximity of *P. vivax* index cases from the prior 2 years. The Loreto region in the Peruvian Amazon was selected as the study site due to its low endemicity of malaria, predominance of *P. vivax*, preliminary data demonstrating cases are primarily subclinical and low density infections, and strong infrastructure to facilitate delivery of fMDA and measure its impact [26]. Importantly, Peru recently approved the use of tafenoquine (TQ), a single dose 8-aminoquinoline which has been shown to be non-inferior to primaquine (PQ) for radical cure, and a new point-of-care test for G6PD deficiency for symptomatic case management. These tools hold promise for facilitating safe and effective delivery of radical cure in communities as part of MDA for *P. vivax* transmission reduction and elimination [27].

### Aims and objectives

The overall study objective is to evaluate the impact and safety of fMDA for *P. vivax* transmission reduction compared to no fMDA. The primary aim is to determine the effect of fMDA on the outcome of cumulative incidence of symptomatic, microscopy-confirmed *P. vivax* cases over the study period. *P. vivax* incidence will be determined based on the number of laboratory-confirmed, locally acquired cases reported from health facilities serving the catchment area of study villages. Secondary outcomes include incidence of *P. falciparum* or *P. vivax* and *P. falciparum* and infection prevalence and seroprevalence of *P. vivax* and/or *P. falciparum* measured in cross-sectional surveys (Table S1). Secondary aims are to assess the safety, tolerability, and acceptability of fMDA, as well as its cost-effectiveness compared to current standard-of-care interventions. Safety and tolerability outcomes will be measured as incidence of adverse events detected through active and passive pharmacovigilance and vomiting after administration. Acceptability will be measured as refusal rates and reported willingness to participate in future fMDA campaigns. Cost-effectiveness will be measured as cost per case averted, or per disability adjusted life year (DALY) averted. We hypothesize that fMDA will result in a greatly reduced latent hypnozoite reservoir and that will translate to reduced incidence, infection prevalence, seroprevalence, and cost-effectiveness compared to standard interventions and that it will be safe, well-tolerated, and acceptable to the community.

## Methods and design

The SPIRIT (Standard Protocol Items: Recommendations for Interventional Trials) recommendations were referenced in developing this protocol [28]. Figure 1 demonstrates the overall study communities’ involvement in the FLAME trial per SPIRIT guidelines.

**Fig. 1 Fig1:**
[figure not shown]
Flowchart demonstrating the involvement of FLAME communities throughout the trial per SPIRIT guidelines. Vector control includes the distribution of insecticide-treated nets (ITNs) and the use of indoor residual spraying (IRS). Symptomatic case management involves testing and treating confirmed malaria cases by microscopy or PCR testing at local health facilities or in the community by a community health worker. Outbreak response may include an active search strategy through screening and treatment of confirmed cases when malaria case incidence is increased significantly compared to the regular trend of cases for 2 consecutive weeks

### Study design

This is a 3-year open-label CRCT, including enrollment, allocation, post-allocation, and close-out phases (Fig. 2). The trial will be pragmatic and implemented through the existing health system. To demonstrate sustained impact in this tropical setting where strains of *P. vivax* relapse earlier than those once found in Central China [29], the fMDA intervention is relatively aggressive at two rounds per cycle, and the implementation period and follow-up will be longer than prior trials [1].

**Fig. 2 Fig2:**
[figure not shown]
SPIRIT schematic to depict the schedule of enrollment, interventions, and assessments. Study years begin in June and end in May. The treatment arm will receive control arm interventions in addition to the treatment arm interventions

### Study setting and trial preparations

The trial will take place in Loreto Department, located in the Peruvian Amazon and where more than 90% of the country’s malaria cases occur [30]. Malaria transmission is perennial and historically peaks around April to June, though recently transmission has leveled out throughout the year. Based on national data from the first half of 2024, 82.5% of reported cases were *P. vivax* [30].

Communities or clusters will be eligible if they are located within 8 h of riverine or road transport of Iquitos. Villages with high (API > 250/1000) or sporadic transmission (< 2 cases) in the year prior to the trial, or extreme population size (> 650) will be excluded. A map of the study area and distributions of recent *P. vivax* annual parasite incidences (API) among communities in the region are shown in Fig. 3.

**Fig. 3 Fig3:**
[figure not shown]
Map of communities within the study area by annual parasite incidence (API) in 2022. API calculated as annual number of malaria cases reported among residents of community per 1000 population. Population data is based on most recent population estimates from 2017 or 2019, depending on the community

Prior to the trial commencing, activities will be conducted to facilitate study implementation and gather baseline epidemiological data. A census and geographic reconnaissance survey was conducted in August 2023 to enumerate the study area and geolocate households. Malaria cases from the 2 years prior to the trial launch will be collated from paper-based malaria registers and NOTIWEB, the electronic malaria case reporting system. Based on these and past census data, cases in individuals residing in the study area will be geolocated to their household.

Prior to the trial launch, the study team will engage in community sensitization, which will consist of meeting with Gerencia Regional de Salud (Regional Management of Health) leadership and engaging with local community leaders, health workers, and villagers. Prior to trial launch, health facilities in both arms will receive refresher trainings regarding case management and case reporting to bolster the strength of the existing health surveillance program and ensure high surveillance data quality across both arms.

### Randomization and masking

The unit of randomization will be a community. A restricted randomization will be conducted taking into consideration *P. vivax* incidence in the prior year, distance to the nearest health post, distance to Iquitos, and population size. The Data Manager will remain unblinded to study arm assignment; however, the trial statistician and data analyst will be blinded to the study arm assignment.

### Procedures

#### Enrollment and a baseline assessment

Individual written informed consent will be sought during the baseline survey or during subsequent surveys for new participants. Verbal consent will be requested separately for each subsequent study procedure, including completion of questionnaires, blood testing, and drug administration. Consent for minors less than 18 years of age will be sought from a parent or guardian, and minor assent will also be sought from participants 8–17 years old. Informed consent will be sought in Spanish.

Enrollment and a baseline assessment in consenting individuals will be sought prior to any intervention implementation activities. At the baseline assessment, demographic, epidemiological, and clinical data will be collected. A finger prick will be conducted for rapid G6PD testing using the STANDARD G6PD test (SD Biosensor, Inc., Suwon, South Korea) per manufacturer’s instructions. G6PD status will be categorized as deficient ($$\le$$ 4.0 IU/g Hb), intermediate (4.1–6.0 IU/g Hb), or normal (≥ 6.1 IU/g Hb), which reflect ranges of enzymatic activity below or near normal activity of 9.0 IU/g Hb [31], respectively. As the STANDARD G6PD test includes a hemoglobin (Hb) measurement, this result will also be recorded. Blood from the same finger prick will also be used to generate a dried blood spot (DBS) for malaria molecular testing and G6PD sequencing to identify variants among G6PD deficient and intermediate individuals and 5% of the G6PD normal individuals. For individuals with fever in the past 48 h, microscopy will be performed by health promoters at health establishments, and treatment will be provided per national policy. Current first-line treatment is artesunate-mefloquine for *P. falciparum* and chloroquine (CQ, 10 mg/kg on days 1 and 2, and 5 mg/kg on day 3) plus PQ (0.5 mg/kg/day × 7 days) for *P. vivax* [32].

#### Standard malaria interventions in the control and intervention arms

As part of the country’s national malaria elimination program, Plan Malaria Cero (Plan Malaria Zero) [26], standard malaria interventions will be provided in both study arms. Led by health promoters, these interventions include passive and active case detection at community members’ homes or at health establishments, microscopy at health establishments, and treatment per national policy guidelines. Tafenoquine (300 mg × 1) is registered in Peru as a radical cure for individuals that are G6PD normal and $$\ge$$ 16 years of age, but it is currently only available in pilot health facilities outside of the study area. Passive case detection detects symptomatic cases at health facilities. Active case detection up to 6–8 times per year involves village-wide searching for fever, followed by treatment of individuals testing positive by microscopy or rapid test. Vector control interventions include provision of Duranet insecticide-treated bed nets (1.5–1.7 people/net) impregnated with alpha-cypermethrin provided every 3 years on average and spraying with pirimiphos-methyl insecticide approximately 2 times per year (78.2% coverage of households in the Maynas Province of the Loreto Department).

#### fMDA in the intervention arm

In the intervention arm, fMDA will be administered over 3 consecutive years. In each cycle, the intervention arm will receive two rounds of fMDA, with each round separated by 2 months and each cycle separated by 9–11 months (Fig. 4). fMDA will be administered by directly observed therapy (DOT) and will target high-risk individuals meeting eligibility criteria detailed in Table 1. These eligibility criteria include being a malaria index case or living in a household within a 200-meter radius of a *P. vivax* index case. The 200-meter radius was selected based on evidence from other cohort studies in the Peruvian Amazon indicating clustering of asymptomatic, submicroscopic infections among neighboring households, generally within 200 meters [33–35]. Index cases will include cases reported in the 2 years prior to the first round of each fMDA cycle detected through passive or active case detection. Individuals with high-risk status will be screened for other inclusion and exclusion criteria for fMDA eligibility.

**Fig. 4 Fig4:**
[figure not shown]
Schematic of the overall study timeline and major activities including surveys and fMDA. Each activity is demarcated with a colored triangle. The grant period includes annual cycles from June to May (orange bars), and the historic peak transmission season includes the period between November and April (purple bars). Abbreviations: NCE = no cost extension

**Table 1 Tab1:** Eligibility criteria for study activities

	Inclusion criteria	Exclusion criteria
Clusters	• Within 8 h transport of Iquitos • Incidence < 250/1000 and > 2 cases in the year prior to trial • Population size (< 650)	• Outside of study area including villages on the banks of the Momon, Nanay, Itaya, and Pintuyacu rivers and along the main road in the region, Carretera Iquitos-Nauta
Study enrollment	• Slept in household within study community at least one night in the past 4 weeks •$$\geq$$ 6 months old • Signed informed consent	
fMDA		
Chloroquine	• Resides in neighboring household but within 200 m of Pv index case in the past 2 years • Age ≥ 6 months old • Present for intervention • Adult ≥ 18 years old that provides informed consent • A child ≥ 8 years and < 18 years old that provides informed assent and has informed consent from their parents • A child ≥ 6 months old and < 8 years old that has informed consent from their parents	• History of retinal or visual field changes • Known hypersensitivity or adverse reaction to CQ • Currently taking CQ or have taken CQ in the past 4 weeks • Ineligible for TQ or PQ (see criteria below) • Hemoglobin < 9 g/dL
Tafenoquine	• Eligible to receive CQ • Age ≥ 16 years old • Adult ≥ 18 years old that provides informed consent • A child ≥ 16 years and < 18 years old that provides informed assent and has informed consent from their parents	• G6PD deficiency or intermediate status (defined as activity $$\le$$ 6.0 UI/gHb per SD biosensor) • G6PD status unknown or refusal of G6PD status test • Acute or severe malaria • Pregnancy (known or identified by pregnancy test) • Refusal of pregnancy test if new amenorrhea in the past 4 weeks • Woman breastfeeding a child that is G6PD deficient or with unknown G6PD status • Known hypersensitivity or adverse reaction to TQ or PQ • Have taken mefloquine (i.e., artesunate-mefloquine), TQ or PQ, or other antimalarial in the past 4 weeks • Hemoglobin < 9 g/dL
Primaquine	• Eligible to receive CQ and ineligible to receive TQ • Age ≥ 6 months old • Adult ≥ 18 years old that provides informed consent • A child ≥ 8 years and < 18 years old that provides informed assent and has informed consent from their parents • A child ≥ 6 months old and < 8 years old that has informed consent from their parents	• G6PD deficiency (defined as activity ≤ 4.0 UI/gHb per SD biosensor) • G6PD status unknown or refusal of G6PD status test • Acute or severe malaria • Pregnancy (known or identified by pregnancy test) • Refusal of pregnancy test if new amenorrhea in the past 4 weeks • Breastfeeding child with documented or unknown G6PD deficiency status • Known hypersensitivity or adverse reaction to TQ or PQ • Have taken mefloquine (i.e. artesunate- mefloquine), TQ or PQ, or other antimalarial in the past four weeks • Hemoglobin < 9 g/dL

Each round of fMDA will include CQ plus either TQ, for non-pregnant individuals $$\ge$$ 16 years of age and G6PD normal, or PQ, for non-pregnant individuals 6 months to 15 years of age and G6PD normal or intermediate. The prevalence of G6PD deficiency in the study area is anticipated to be < 5% [36–40]. Preliminary data from the study area shows that 36.2% of the study population is > 6 months and < 16 years and will receive PQ. If pediatric TQ is approved for use in Peru during the study, its use will be incorporated into the study.

For the first annual rounds (referred to as 1a, 2a, and 3a for years 1, 2, and 3, respectively) the regimen will include 3 days of CQ (10 mg/kg on days 1 and 2, and 5 mg/kg on day 3) for treatment of *P. vivax* asexual blood stages, with TQ or PQ for *P. vivax* hypnozoite stages (TQ 300 mg × 1 or PQ 0.5 mg/kg/day × 7 days) (Table 2). PQ and TQ provide prophylactic and gametocytocidal effects against both *P. vivax* and *P. falciparum* [41–45]. However, compared to PQ which has a short half-life of roughly 4–9 h [46–48], TQ will provide an extended period of protection given its prolonged terminal elimination half-life (~ 15 days), the time it takes to reduce the plasma concentration of TQ by 50%. This will provide post-treatment prophylaxis for up to 77 days [49, 50].

**Table 2 Tab2:** Drugs formulations and doses for all fMDA Rounds

**Drug***	**Dosage form (mg)**	**Administration**	**Manufacturer**	**Dose**	
				**≥16 years**	**6 mos – 15 years**

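### Table 1's refusal rule for the pregnancy test (tafenoquine and primaquine) misses a breastfeeding woman whose periods have not returned, because her amenorrhea is not new

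*Protocol article*

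**What the plan says.** The text after Table 1 in the section on fMDA in the intervention arm sets the target group: "Each round of fMDA will include CQ plus either TQ, for non-pregnant individuals" who are at least 16 years old and G6PD normal, or PQ for younger non-pregnant people who are G6PD normal or intermediate. Tables 1 and 2 also allow PQ from age 16 when TQ cannot be given.

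Table 1 turns this into exclusions. The TQ and PQ cells carry the same two pregnancy lines:

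- "Pregnancy (known or identified by pregnancy test"
- "Refusal of pregnancy test if new amenorrhea in the past 4 weeks"

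Breastfeeding has its own line in each cell. For TQ it is "Woman breastfeeding a child that is G6PD deficient or with unknown G6PD status"; for PQ it is "Breastfeeding child with documented or unknown G6PD deficiency status". The chloroquine (CQ) cell excludes anyone "Ineligible for TQ or PQ (see criteria below", so a person barred from both 8-aminoquinolines gets no study drug at that round.

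The article does not define new amenorrhea and says nothing about amenorrhea during breastfeeding.

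**The concern.** The first pregnancy line cannot detect a pregnancy that is both unrecognised and untested. That leaves the refusal line as the only printed safeguard for a woman who declines the test, and it applies only if her amenorrhea is new. Long-standing amenorrhea does not rule pregnancy out, least of all during breastfeeding, when ovulation can resume before the first period.

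Table 1 treats the parallel G6PD question more strictly: unknown status, or refusal of that test, excludes without any further condition. A nursed child of unknown G6PD status also excludes the mother. A fetus would likewise be of unknown status, yet refusing the pregnancy test excludes only with a qualifier.

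At stake is fetal exposure to a drug that the plan bars in pregnancy. TQ is one 300 mg dose with a stated half-life of about 15 days, so it cannot be withdrawn once given. The protocol lists congenital anomaly among its serious adverse events. Declining one procedure and accepting another is foreseeable, because the enrolment section seeks verbal consent separately for each study procedure.

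**Working it through.** No arithmetic applies. The check is to take a woman who declines the test, accepts the drug and is not known to be pregnant, and to apply every printed line that could exclude her on these grounds.

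Two readings of the refusal line are possible:

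- **Onset reading:** the amenorrhea began within the past 4 weeks.
- **Look-back reading:** she has had no menses over the past 4 weeks, and this is a change from her usual pattern.

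| Woman who declines the test | Pregnancy line | Breastfeeding line | Refusal line, onset reading | Refusal line, look-back reading |
|---|---|---|---|---|
| 1. Amenorrhea that began within 4 weeks | no | no | excluded | excluded |
| 2. Not breastfeeding, periods stopped more than 4 weeks ago | no | no | not excluded | excluded |
| 3. Breastfeeding a child who is G6PD deficient or of unknown status | no | excluded | not needed | not needed |
| 4. Breastfeeding a child with a known non-deficient result, no period since the birth | no | no | not excluded | not excluded |

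**Row 2** depends on the reading. The situation can arise within a cycle, since the plan has "two rounds of fMDA, with each round separated by 2 months". That gap is longer than 4 weeks, so amenorrhea starting soon after one round can be older than 4 weeks at the next.

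**Row 4** does not depend on the reading. Her amenorrhea dates from the birth, or from the pregnancy before it, so it is not new in either sense. She would be excluded only if the word *new* were ignored.

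**Who falls in row 4.** The study enrolment row of Table 1 sets an age floor ("6 months old • Signed informed consent"). A child with a G6PD result from the study is therefore at least 6 months old. A younger infant would probably be of unknown status, which moves the mother to row 3. Row 4 is thus limited in practice to women nursing an older infant or child who has been tested.

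**Which drug.** From age 16 with normal G6PD, the woman in row 4 would receive TQ. With intermediate activity (4.1 to 6.0 IU/g Hb) she is barred from TQ but not from PQ, whose cut-off is 4.0 or below. The refusal line is identical in the PQ cell, so the gap exists there too.

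**The case against.** The case on the other side has four parts.

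1. *The look-back reading is the more natural one.* Other lines of Table 1 use the same 4-week phrase as a look-back window, for nights slept in the household and for recent antimalarial use. This stands for row 2. A reader might infer that every woman with amenorrhea longer than 4 weeks escapes the rule. The text does not support that: on the look-back reading such a woman is covered, and what remains is an ambiguity. Row 4 is unaffected.

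2. *The chain of events is long.* Harm requires a woman in a focal zone who is nursing a tested, non-deficient child, has had no period since the birth, has conceived without knowing it, declines the test and accepts the drug. This stands. It limits the size of the problem and does not close the gap. A reader might also want to infer a sizeable number affected, but the document gives no rate of test refusal, breastfeeding or pregnancy from which to calculate one.

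3. *The full protocol may settle it.* The trial runs on a Spanish protocol that is not shown, and who is tested and how menstrual history is taken normally belong there. This stands in part. The point says nothing about actual practice, and it would be wrong to infer that pregnant women are being dosed. But the article does print a specific rule, and that rule falls short of its own restriction to non-pregnant people.

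4. *A stricter rule costs coverage.* The discussion names high coverage as a key challenge, and those excluded also lose CQ. A rule drafted too broadly could also catch premenarchal girls, because the PQ cell covers children from 6 months. Both are reasons to draft the rule narrowly. Neither is a reason to keep the word *new*.

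**Conclusion.** The point holds as a minor, cheap safety improvement to the eligibility wording. On the printed text, a woman breastfeeding a child with a known non-deficient G6PD result, without a period since the birth, can decline the test and still receive TQ or PQ with pregnancy status unknown. For other women with amenorrhea longer than 4 weeks, the wording is unclear and need not be wrong.

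The affected group is small and its size cannot be derived from the document. The conclusion assumes that *new* is given its ordinary meaning and that no unseen procedure overrides the table. A reader might infer a threat to the trial's result; there is none, because the primary outcome is analysed from cluster-level case counts by randomised arm, whatever drug an individual received.

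**What to change.** For any round not yet delivered, replace the refusal line in both the TQ and the PQ cell with:

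*Refusal of pregnancy test in a post-menarchal female of childbearing potential (not postmenopausal or surgically sterile) with no menses in the past 4 weeks, whatever the duration and including during breastfeeding.*

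This removes the dependence on *new*, settles the two readings in favour of the look-back, covers the breastfeeding case and leaves premenarchal girls outside the rule. If the Spanish protocol already says this, only the published table needs correcting.

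The cost is a minor amendment to the eligibility wording during a running trial, with a matching change to the screening form. A few decliners would receive no fMDA drug at that round, including CQ, unless they accept the test.
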